### Statistical analysis

The study will be analyzed by the modified intention-to-treat method, whereby all randomized patients who had at least one post-baseline measurement of proteinuria will be included in the primary analysis population. Data will be presented descriptively by means and standard deviations, or with absolute and relative frequencies, according to the respective scale of measurement. The difference between the groups in the change from baseline in the primary efficacy variable will be tested by analysis of covariance with a multiple linear regression model, with the baseline value entered as covariate, *Diabetes mellitus* entered as stratification variable, and study group as independent variable. For secondary efficacy variables, in those measured in an interval scale, the change from baseline will be compared between groups with the same method. For those variables that are related to patient sex (e.g., WC, sarcopenia), sex will be included as independent variable. For variables measured in ordinal scales, only the values observed in the last valid observation will be considered and will be compared between groups with the Wilcoxon-Mann-Whitney U test. No multiplicity correction of p-values will be applied to the secondary variables.

Statistical analyses will be performed using Stata 15.1 (Stata Corp., Collegue Station, TX). Tests with two-sided p values < 0.05 will be considered statistically significant.

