**Discussion:**

The study will assess the effects of an individualized nutritional intervention on proteinuria 12 months after KTx.

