### Primary and secondary efficacy variables

The primary and secondary efficacy variables defined for the study are described in Table 1.

**Table 1 pone.0272484.t001:** Description of the primary and secondary efficacy variables for patients who have received a KTx and participated in the study.

Primary efficacy variable	Secondary efficacy variable
**• Change from baseline in log proteinuria (urinary albumin/creatinine ratio)**	• Change from baseline in the body adiposity percentage
	• Change from baseline in lean body mass
	• Change from baseline in body mass index
	• Difference in quality of life and physical activity
	• Change from baseline in lipid profile (triglycerides, total cholesterol, high-density lipoprotein cholesterol and low-density lipoprotein cholesterol)
	• Change from baseline of glycemic control (fasting glucose and glycated hemoglobin).

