### Sample size and recruitment

The sample calculation was performed using the software Stata 15.1 (Stata Corp., College Station, TX), based on a published study of patients who had undergone KTx with a mean log proteinuria of 2.36 mg (standard deviation of 1.55) at 6 months, by the urinary albumin/creatinine ratio [17]. To demonstrate a difference of 25% in the geometric mean of proteinuria at 6 months between the trial groups, with α error of 5% (α ≤ 0.05) and statistical power of 70%, 87 patients per study group will be needed. Assuming a drop-out rate of 5% prior to the first follow-up visit, the sample size is set at 92 subjects per group. Recruitment is scheduled to take place from May 1, 2019 through to December 31, 2022.

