### Nutritional intervention

Participants randomized to the intervention group will be subjected to an individualized nutritional intervention prescribed after 60 days of KTx by a professional nutritionist participating in the research through an individualized plan with a two-option substitution rate calculated with the aid of the *Virtual Nutri Plus 2*.*0* software, using nutritional recommendations for the late post-KTx period, according to Table 2 [10, 11]. The foods and preparations on the plan will be presented in the form of weights and conventional homemade measures [19, 20] that the patients are familiar with in their routines. In order to gain a better understanding of the diet plan, photographic records of portions of food [21] and real-sized food models made of silicone will be used as illustrations for demonstrating the portions suggested in the menu.

**Table 2 pone.0272484.t002:** Nutritional recommendations for food planning in the late post-KTx period.

Nutrient	Nutritional recommendation
Energy	25–30 kcal/kg/day
Protein	1.0 g/kg
Total lipids	< 30% of the total kcal
Saturated fatty acids	< 10% of total calories
Monounsaturated fatty acids	10–15% of total calories
Polyunsaturated fatty acids	≥ 10% of total calories
Cholesterol	< 300mg
Carbohydrates	50% of total kcal
Fiber	25–30 g
Sodium	3–4 g
Potassium	Restricted (1–3g) only if hyperkalemia and/or oliguria are present
Phosphorus	1200–1500 mg
Calcium	800–1500 mg
Iron	The need for supplementation depends on the body reserves
Magnesium	Supplementation, if required, while using cyclosporine
Water-soluble vitamins	Usually no need for supplementation
Vitamin D3	1 a 2 μg, if required

Source: Martins; Pecoits-Filho; Riella [10]. Riella; Martins [11].

Patients randomized to the control group will receive nutritional guidance for the post-transplant period as offered by the hospital. The guidelines manual will be prepared based on literature [10, 11] and will have information and suggestions for weight and blood lipid and glucose control, attention to the intake of foods that are sources of fat, sodium and general guidelines on healthy, safe eating and food recipes.

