### Evaluation and analysis of biochemical parameters

The urinary albumin/creatinine ratio will be evaluated from the first morning urine samples to assess albuminuria. Urinary albumin and creatinine concentrations will be determined using Wiener kits using the CMD-800 (Wiener Laboratories, Rosario, Argentina).

Blood samples will be taken after a 12-hour fasting period. Blood biochemical parameters will be performed by means of urea, creatinine, uric acid, triglycerides, total cholesterol, high-density lipoprotein cholesterol, low-density lipoprotein cholesterol, as well as, fasting glucose, basal insulin, and glycated hemoglobin will be evaluated. Other parameters will be evaluated, such as serum concentrations of total proteins, albumin, total calcium, phosphorus, sodium, potassium, magnesium, total alkaline phosphatase activity, parathyroid hormone (PTH), 25-hydroxyvitamin D [25(OH)D] and tacrolimus concentrations.

The urea, creatinine, uric acid, triglycerides, total cholesterol, high-density lipoprotein cholesterol, low-density lipoprotein cholesterol, fasting glucose, glycated hemoglobin, total proteins, albumin, total calcium, phosphorus, sodium, potassium, magnesium, total alkaline phosphatase will be evaluated in blood samples using *Wiener* kits according to the methodology described by the manufacturer, using the *CMD-800* biochemical analyzer (*Wiener Laboratories*, *Rosario*, *Argentina*). Further, PTH, 25(OH)D, basal insulin and tacrolimus concentrations will be measured by the chemiluminescence method with ABBOTT^®^ kits, using the ARCHITECT i2000SR Immunoassay *Analyzer (ABBOTT Diagnostics*, *Illinois*, *USA*).

All biochemical analyzes will be performed at all the time points in the study (T0, T3, T6, T9, and T12 after KTx).

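### The primary endpoint has no single time point: the trial is sized at 6 months, the stated aim is 12 months, and the primary test names no visit

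*Protocol article*

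**What the plan says.** - **Endpoint (Table 1, Primary and secondary efficacy variables):** "Change from baseline in log proteinuria (urinary albumin/creatinine ratio". No visit is attached.
- **Sample size (Sample size and recruitment):** "To demonstrate a difference of 25% in the geometric mean of proteinuria at 6 months between the trial groups". The mean (2.36) and SD (1.55) of log proteinuria are also 6-month values. The 5% drop-out allowance covers only losses before the first follow-up visit.
- **Aim (Abstract, Discussion):** "The study will assess the effects of an individualized nutritional intervention on proteinuria 12 months after KTx".
- **Measurement schedule (Evaluation and analysis of biochemical parameters):** "All biochemical analyzes will be performed at all the time points in the study (T0, T3, T6, T9, and T12 after KTx". Each patient can therefore have four post-baseline values.
- **Primary test (Statistical analysis):** the group difference in change from baseline "will be tested by analysis of covariance with a multiple linear regression model, with the baseline value entered as covariate", plus the diabetes stratum and study group. No visit or repeated-measures term is mentioned.
- **Primary population (Statistical analysis):** "all randomized patients who had at least one post-baseline measurement of proteinuria will be included in the primary analysis population".
- **Start of the diet (Nutritional intervention):** "individualized nutritional intervention prescribed after 60 days of KTx".

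**The concern.** A change-from-baseline endpoint is fully defined only when the follow-up visit is named. Here two visits are implied in different places, and the two places that should settle the matter, the endpoint definition and the primary test, name none. An analyst could take month 6, month 12 or some summary of several visits and justify each choice from the text. Each can give a different primary p-value. Because the trial is open-label, the choice should not remain open once data by group can be seen.

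The population adds a second, smaller difficulty. It admits anyone with one post-baseline value at any visit, while the test as described takes one change per patient. Patients who leave after month 3 belong to the population but have no observed value at month 6 or month 12. Such patients are foreseeable: the Treatment adherence section ends participation for several events that can occur during follow-up.

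**Working it through.** **1. The time points side by side**

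| Place in the article | Time point |
|---|---|
| Sample size and recruitment | 6 months |
| Abstract, Discussion | 12 months after transplantation |
| Table 1 | none |
| Statistical analysis | none |
| Biochemical parameters | T0, T3, T6, T9, T12 all measured |

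The main Discussion leans towards 12 months: it describes a 12-month intervention and cites proteinuria at 1 year as a prognostic marker.

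**2. Reproducing the plan's own figure**

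Inputs from Sample size and recruitment: mean 2.36, SD σ = 1.55, α = 5%, power 70%. The Statistical analysis section gives two-sided testing. The stated number is recovered when the difference is 25% of the mean log value, δ = 0.25 × 2.36 = 0.59. (Whether that is the right translation of a 25% difference in geometric means is a separate point.)

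n = 2(1.960 + 0.524)² σ² / δ² = 2 × 6.17 × 2.4025 / 0.3481 ≈ 85.2, so 86 by the normal formula. The t-based calculation gives 87. Then 87 / 0.95 = 91.6, so 92.

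The 87 and 92 are thus 6-month figures. The article gives no 12-month mean or SD, so power at month 12 cannot be computed from it.

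**3. Illustration: one fixed visit, observed values only**

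Assume, without support in the document, that δ = 0.59 and σ = 1.55 also hold at month 12. With total loss L from 92 per group, n = 92(1 − L), and power = Φ(δ / (σ√(2/n)) − 1.960).

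For L = 20%: n = 73.6; standard error = 1.55 × √(2/73.6) = 0.2555; 0.59 / 0.2555 = 2.309; Φ(0.349) = 0.64.

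| Total loss | 5% | 10% | 15% | 20% | 30% |
|---|---|---|---|---|---|
| Power | 71% | 69% | 66% | 64% | 58% |

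Only the 5% column corresponds to a loss the plan allows for.

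**4. Illustration: each patient's last available value**

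Month 3 is about 90 days after transplantation and the diet starts after day 60, so a month-3 value reflects about one month of intervention. Suppose, hypothetically, that the effect is 25%, 50%, 75% and 100% of its final size at T3, T6, T9 and T12, and that early last values are spread evenly over T3, T6 and T9. Their average effect is (25 + 50 + 75)/3 = 50%.

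- 10% early last values: 0.90 × 100% + 0.10 × 50% = 95% of the month-12 effect.
- 20%: 0.80 × 100% + 0.20 × 50% = 90%.

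At 87 per group with σ unchanged, δ becomes 0.95 × 0.59 = 0.5605 (power 66%) or 0.90 × 0.59 = 0.531 (power 62%). These figures assume equal losses in both groups; unequal losses could bias the estimate in either direction.

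**The case against.** **An unseen analysis plan may settle this.** That is a fair answer for missing-data handling. An analysis set requiring one post-baseline value is common, and the lack of an imputation rule or repeated-measures term in an article is not in itself a fault. It does not answer the time point: the article states two, and any later plan must depart from one of them.

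**The 12-month sentence is a one-line summary, and month 6 is the only visit with a design mean and SD.** This stands as an argument about which visit to choose. Naming either visit would cure the contradiction.

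**Stronger readings that the document does not support.**

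- A reader might infer that the plan carries the last value forward for the primary endpoint. It does not say so. The rule that "only the values observed in the last valid observation will be considered" is given for ordinal variables, and the primary variable is not ordinal. Last available value is one possible reading.
- A reader might infer that a one-value ANCOVA can hold the whole population in no other way than by mixing visits, or that the remaining visits go unused. Neither is stated. Multiple imputation to a fixed visit would keep everyone.
- A reader might expect a marked gain in precision from four visits. That gain belongs to an effect averaged over visits. For a contrast at one visit with complete data, a repeated-measures model gives essentially the ANCOVA estimate; earlier visits help mainly through patients who miss that visit.

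**The bias is modest.** On the assumptions shown, 90% to 95% of the effect survives. That is true, and the assumptions are hypothetical.

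**Conclusion.** The point holds for the time point, and it must be resolved before analysis: 6 months in the sizing, 12 months in the aim, and no visit in the endpoint or the test. This rests on the text alone and needs no assumption.

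The mismatch between population and model is real but secondary. A fixed-visit ANCOVA of observed values would leave out part of the stated population, and using whatever value exists would mix month-3 with month-12 values. The document does not say which is intended.

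The numerical consequence cannot be fixed from the document, because it gives no month-12 mean or SD and no loss rate after the first visit. The power figures (69% and 64% at 10% and 20% total loss) assume that the 6-month inputs carry over. The 90% to 95% figures assume a steadily growing effect and evenly spread losses. They show the likely order of the problem and are not estimates for this trial.

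**What to change.** By dated amendment, before outcomes are examined:

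1. Name one primary visit, in the same words, in the abstract, Table 1, Sample size and recruitment, and Statistical analysis. Month 12 matches the stated aim; month 6 would then be secondary.
2. State that 87 (92 with drop-out) per group is a 6-month calculation and that no 12-month mean or SD is given.
3. Match the model to the population: a mixed model for repeated measures on the log ratio at T3, T6, T9 and T12, with arm, visit, arm × visit, baseline log ratio × visit and diabetes stratum, and the primary contrast at the named visit. This includes every patient in the stated set without carrying values forward. ANCOVA at the named visit with a stated multiple-imputation method is an acceptable alternative.

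The cost is a formal amendment, since recruitment began in May 2019, together with revised analysis wording and code. No new data are needed. The downside of choosing month 12 is that the stated 70% power is only assumed to carry over, and it falls with losses after the first visit.

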### Randomization

Randomization will be by permuted blocks of varying size and stratified by diagnosis of *Diabetes mellitus*. Two randomization lists, one for each stratum, will be generated from the *randomization*.*com* website [18]. From the randomization lists, two sets of sequentially numbered opaque envelopes will be created, containing the identification of the trial groups. As the nutritional intervention will be tailored to the treatment group, there is no possibility of blinding.

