### Quality of life assessment and physical activity

Participants in the case and control groups will be assessed for quality of life, using the generic questionnaire *Medical Outcomes Study 36-Item Short-Form Health Survey (SF-36)* translated and validated into Portuguese and applied in three periods T0, T6, and T12 after KTx [27]. The instrument consists of 36 items or questions, encompassed in eight domains and summarized into physical and mental components. The score for each domain ranges from 0 (worst health) to 100 (best health). The data analysis for tabulation will be performed through registration on an online platform through the website *qualipes*.*com*.*br* [38] by the same evaluator in all the stages of the study.

Considering that depression, anxiety, and other mental disorders can directly affect the quality of life of individuals, an interview will be conducted with the *Self-Reporting Questionnaire (SRQ-20)* [28], which is the Brazilian version of a psychiatric screening questionnaire that assesses non-psychotic mental disorders in the primary health care system, consisting of 20 items that can be answered as “Yes” or “No” with scores ranging between 7 and 8 points for men and women, respectively.

In addition to the previous parameters, the levels of physical activity of the patients will be assessed using the full version of the *International Physical Activity Questionnaire (IPAQ)*, translated and validated in Portuguese [29]. The IPAQ considers the activities carried out in the last seven days under four domains: means of transport, housework and recreation, sports, and leisure. The final score will be converted to MET-minutes/week. Assessment of physical activity will always be carried out by the same evaluator.

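### Ordinal outcomes are compared on the last valid observation, at no fixed visit, by a rank test that drops the baseline value and the diabetes stratum

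*Protocol article*

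**What the plan says.** The Statistical analysis section of the protocol article sets two routes for secondary variables.

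- **Interval-scale variables** use the same method as the primary variable: analysis of covariance of the change from baseline, "with the baseline value entered as covariate, *Diabetes mellitus* entered as stratification variable, and study group as independent variable". Diabetes is also the factor by which randomization is stratified (Randomization section).
- **Ordinal variables** follow a different rule: "For variables measured in ordinal scales, only the values observed in the last valid observation will be considered". These values "will be compared between groups with the Wilcoxon-Mann-Whitney U test". No visit is fixed, a valid observation is not limited to post-baseline visits, and no covariate or stratum is named.

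The only analysis population described is defined by proteinuria: "all randomized patients who had at least one post-baseline measurement of proteinuria will be included in the primary analysis population". Proteinuria is measured often: "All biochemical analyzes will be performed at all the time points in the study (T0, T3, T6, T9, and T12 after KTx". The SF-36 is measured less often: it is "applied in three periods T0, T6, and T12 after KTx".

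Table 1 words every secondary variable as a change from baseline except one entry: "Difference in quality of life and physical activity". The article does not list which variables it regards as ordinal.

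**The concern.** Taking each patient's last available value, whatever its visit, is last observation carried forward. It has three consequences.

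1. The compared values can come from different visits, so the result describes no single point in time.
2. Nothing in the wording stops a T0 value from being the last valid one. T0 is the immediate post-transplant assessment (Trial design), and the diet is prescribed after 60 days (Nutritional intervention). A T0 score therefore cannot reflect the intervention.
3. Baseline and diabetes are recorded for these patients and are used for the other variables, but not here.

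Quality of life is part of the stated aim of the study. If the ordinal rule governs it, the trial would test that question with less precision than its own data allow, and the answer would be harder to interpret.

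**Working it through.** **Can T0 become the outcome?** Take a patient with a T3 urine sample who leaves before T6. The patient has a post-baseline proteinuria value and so meets the population definition. The SF-36 schedule has nothing between T0 and T6, so the only SF-36 score is T0. If the SF-36 is treated as ordinal and the same population is used, the wording permits T0 as the outcome. It does not say that this will be done.

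**Group size used below.** The article gives no power figure for ordinal outcomes. Its 87 per group is for the primary variable. It is reproduced by reading the 25% as a quarter of the mean log value: 0.25 × 2.36 = 0.59; n = 2 × (1.960 + 0.524)² × 1.55² / 0.59² = 85.2, so 86, or 86.17 (87) with the t distribution. Then 87 / 0.95 = 91.6, so 92. Here 87 serves only as the group size.

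**Cost of dropping the baseline, continuous score.** Assumed: true difference 0.4 SD, normal scores, two-sided 5%, baseline correlation r.

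- Standardised signal of an unadjusted comparison of means: 0.4 × √(87/2) = 2.638.
- Rank test: multiply by √(3/π), giving 2.578. Power = Φ(2.578 − 1.960) = 0.73.
- Covariance adjustment: divide 2.638 by √(1 − r²). At r = 0.3 this is 2.766, power 0.79. At r = 0.5 it is 3.046, power 0.86.

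Simulation (2,000 runs) agrees:

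| r | Rank test | Adjusted | Gain |
|---|---|---|---|
| 0.3 | 0.713 | 0.773 | 6.0 points |
| 0.5 | 0.732 | 0.857 | 12.5 points |
| 0.6 | 0.747 | 0.909 | 16.2 points |
| 0.7 | 0.731 | 0.955 | 22.4 points |

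The true rank-test power does not depend on r; the differences in that column are simulation noise.

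**Five-level ordinal score.** Assumed: latent effect 0.38 SD, 30% with diabetes, diabetes effect 0.3 SD, 3,000 runs. The planned test is compared with a rank analysis adjusted for baseline and diabetes that uses post-baseline values only.

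| r | Share with T0 only, per arm | Planned test | Adjusted |
|---|---|---|---|
| 0.3 | 0% | 0.634 | 0.670 |
| 0.5 | 0% | 0.655 | 0.752 |
| 0.3 | 5% | 0.614 | 0.661 |
| 0.5 | 5% | 0.600 | 0.722 |
| 0.3 | 20% | 0.458 | 0.580 |
| 0.5 | 20% | 0.463 | 0.649 |

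Without any carry-forward the gain is 3.6 points at r = 0.3 and 9.7 at r = 0.5. With 20% carried forward from T0, the planned test loses a further 17.5 to 19 points. The adjusted analysis also loses 9 to 10 points from the smaller sample, so roughly half of that loss is due to the rule itself.

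**False positives.** Assumed: no treatment effect, r = 0.5, and a common improvement of 0.5 SD from T0 to T12.

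- T0-only shares of 5% in both arms: type I error 0.053.
- 5% against 15%: 0.053 (simulation standard error about √(0.05 × 0.95 / 3000) = 0.004).
- 5% against 25%: 0.087, against 0.050 for the adjusted post-baseline analysis. The spurious shift is 0.5 × (0.25 − 0.05) = 0.10 SD.

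**The case against.** The strongest reply is that the rule may not reach quality of life at all. The article describes SF-36 domains as scored from 0 to 100 and the IPAQ as MET-minutes per week. Both can be read as interval-scale, and both would then already receive the baseline- and diabetes-adjusted model. The remaining Table 1 variables are plainly interval, so on this reading the ordinal rule touches no listed secondary efficacy variable. This stands as a limit on reach. It also shows that the text needs to say which route applies.

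A reader might infer that the plan carries T0 forward as an outcome. The documents do not say so. The wording leaves it open, and the definition of a valid observation may sit in an analysis plan not shown. The example also relies on the specific SF-36 schedule, whereas the Trial design section lists quality of life at each visit. The only dropout figure, 5%, concerns loss before the first follow-up visit. Those patients have no post-baseline proteinuria and fall outside the population, so no rate for loss between T3 and T6 is given.

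A reader might also infer that the rank test is invalid. It is not: its type I error holds when T0-only shares are similar between arms. Finally, the effect sizes and correlations are assumptions. T0 comes just after surgery, so a weak correlation with month 12, and hence the smaller gain, is plausible.

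**Conclusion.** The point holds in a limited form. The article does fix a last-valid-observation rule with an unadjusted rank test for ordinal variables, and this departs from the adjustment it uses elsewhere. The usual cost is power and interpretability on secondary outcomes.

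Under the assumed inputs with 87 per arm, omitting the adjustment costs about 6 points of power at r = 0.3 and 12 to 13 at r = 0.5 for a continuous score. For a five-level score, where the adjustment also includes diabetes, the cost is about 4 and 9 to 10 points. Any T0 values carried forward dilute the contrast further, by an amount the documents do not allow one to estimate. A spurious difference requires dropout that differs clearly between arms or is informative. That is conceivable in an unblinded trial with rules for premature termination, but it is not shown.

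All of this is conditional on the rule applying to quality of life and physical activity. The primary analysis is unaffected. The change should be made because it is specific and nearly free.

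**What to change.** 1. State that SF-36 domain and component scores and IPAQ MET-minutes are analysed with the baseline- and diabetes-adjusted model already planned for interval-scale variables, at T12. For the SF-36, T6 and T12 could instead enter one repeated-measures model.
2. Name any variables that are truly ordinal. For these, replace the last-valid-observation rule with the T12 value, analysed by a proportional-odds model or a stratified rank analysis of covariance, with baseline value and diabetes included.
3. State that only post-baseline values of the variable being analysed count as outcomes.
4. Align the Table 1 wording for quality of life and physical activity with the chosen analysis.

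The cost is a few sentences and slightly more analysis work with standard Stata commands. No new data are needed. A proportional-odds model brings an assumption that has to be checked.
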